One of the earliest developed scalable psychological interventions was problem management plus (PM+),^17^ which aimed to allow for mental health services to be delivered in places with limited mental health resources. PM+specifically targets people experiencing moderate levels of psychological distress and aims to relieve symptoms related to common mental disorders. The intervention is composed of evidence-based strategies related to problem-solving and behavioural activation and consists of four core components: (1) managing stress, (2) managing problems, (3) get going, keep doing, and (4) strengthening social support.^17^ Several studies have demonstrated the effectiveness of PM+ in adults residing in low-income and middle-income countries through individual ^18 19^ and group formats.^20^,^22^ More recently, the feasibility and effectiveness of the intervention in HICs among refugees have been explored in the Netherlands^23^ and Switzerland.^24^ Although no active ingredients targeting post-traumatic stress symptoms are included in the intervention, PM+ has been shown to reduce individual symptoms of PTSD.^25^ The emotional processing (EP) Theory proposes that effective psychosocial interventions to treat PTSD should include direct modification of the fear structure, which may give rise to symptoms of the disorder, by activating the fear structure using exposure and by integrating more realistic, non-threatening information into it.^26^ Further, recent evidence indicates that processing positive memories and imagining positive events in the future can positively affect mental health outcome.^27^ Given the pervasiveness of experienced traumatic events and PTSD in refugee populations, including in children and adolescents,^5^ it would be worthwhile exploring further whether exposure to memories of negative past events adds to the efficacy of a scalable intervention such as PM+ in reducing symptoms of PTSD and depression, and additionally as to whether it would be feasible to deliver active ingredients of exposure therapy using scalable psychological interventions. To further elucidate the contribution of the retrieval of negative memories in reducing PTSD symptoms, this study seeks to preliminarily compare PM+ with PM+ including an EP component (PM+EP).^28^ The primary aim of this feasibility randomised controlled trial (RCT) study is to evaluate the feasibility and acceptability of the PM+EP and PM+ interventions for forcibly displaced youth residing in Sweden. A secondary aim of this work is to preliminarily compare PM+ with an EP component with PM+ and care of usual.

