### Trial design

The study consists of two phases: a feasibility RCT and a qualitative process evaluation. The feasibility RCT uses a three-armed single-blind randomised controlled parallel group design, comparing PM+, PM+EP and care as usual (CAU) for forcibly displaced persons living in Sweden. We aim to recruit 60 participants who screen positive for moderate psychological distress. Assessments will be conducted at baseline, 1 week after treatment completion (7 weeks) and 3 months after treatment completion (19 weeks). The flow chart of the trial is shown in figure 1. As part of the qualitative process evaluation, we will be exploring beneficiaries’ and implementers’ experiences with the intervention, and practitioners’ and policymakers’ thoughts on the use of PM+/PM+EP more widely in Sweden.

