### Sample size

Since this is a pilot feasibility trial, no formal power calculations have been carried out. A total number of 60 forcibly displaced youth (20 in each arm) will be included in the study, allowing us to evaluate the feasibility and acceptability of the intervention in the proposed setting, as well as drop-out rates for a future definitive trial. This sample size was determined to be sufficient based on prior similar studies.^44 45^

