### Analysis plan

The primary analyses for the feasibility RCT are planned to understand the safety and acceptability of the intervention and to preliminarily understand the within-group changes prior to and following the PM+(EP) Interventions. To accomplish this, both quantitative and qualitative methods will be used. The data will be analysed for the primary outcome and the other continuous measures using repeated measures analysis of variance. Kruskal-Wallis tests will be used if the normal distribution assumption fails. For the feasibility evaluation, intervention-specific analysis (fidelity, attendance to sessions) will be carried out. The qualitative process evaluation data will be analysed following thematic analysis through NVivo Scientific Software. To estimate potential effectiveness for a future trial, intention-to-treat analyses will be employed. Cohen’s d, based on pooled SD, will be used to calculate the treatment effect size of the PM+EP (based on primary outcome).

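### Kruskal-Wallis is the wrong fallback for a repeated-measures ANOVA, and that ANOVA is complete-case by default, which sits badly with the intention-to-treat statement

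*Protocol article*

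**What the plan says.** In the protocol article, the Analysis plan states: "The data will be analysed for the primary outcome and the other continuous measures using repeated measures analysis of variance". The next sentence gives the fallback: "Kruskal-Wallis tests will be used if the normal distribution assumption fails". It does not say which groups the fallback would compare (visits or arms), or on which score.

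The same section gives one purpose of the primary analyses as to "preliminarily understand the within-group changes prior to and following the PM+(EP) Interventions". It then says: "To estimate potential effectiveness for a future trial, intention-to-treat analyses will be employed". The article names no method for missing scores.

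The Introduction gives a between-arm purpose as well: "A secondary aim of this work is to preliminarily compare PM+ with an EP component with PM+ and care of usual". Trial design sets three assessments: baseline, 7 weeks and 19 weeks. Sample size states: "A total number of 60 forcibly displaced youth (20 in each arm) will be included in the study". Feasibility measures sets completion of assessments above 85% as a success criterion.

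**The concern.** The fallback does not match the model it replaces. Repeated-measures ANOVA uses the link between one person's scores over time. Kruskal-Wallis assumes that all observations are independent and has no term for person, visit or baseline. If normality is judged to fail, which is quite possible with 20 people per arm and bounded symptom scales, the analysis moves to a test that does not answer the same question. Because the text does not say what is compared, two analysts could run different tests and both claim to follow the plan.

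The ANOVA raises a second issue. In its classical form it needs every score from every person. The trial would count itself feasible with up to about 15% of assessments missed, so incomplete series are to be expected. Unless scores are imputed, the estimates meant to inform a future trial would come from those who attended every visit, not from all who were randomised.

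**Working it through.** The plan has no power or sample-size figure to reproduce; 3 × 20 = 60 is consistent.

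**1. Kruskal-Wallis across visits, within one arm**

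Inputs: n = 20 per arm and three visits (article). Assumed: equal within-person correlation ρ of 0.3, 0.5 or 0.7; multivariate normal scores; a drop of 0.5 SD at both follow-ups for power; two-sided 5% level. Simulation with 10,000 runs:

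| ρ | Type I error, Kruskal-Wallis | Type I error, Friedman | Power, Kruskal-Wallis | Power, Friedman |
|---|---|---|---|---|
| 0.3 | 1.65% | 5.4% | 26% | 34% |
| 0.5 | 0.55% | 5.5% | 22% | 47% |
| 0.7 | 0.08% | 5.0% | 17% | 70% |

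Separate simulations agree. At ρ = 0.7 they put the Kruskal-Wallis type I error between 0.02% and 0.08%, so the overall range is about 0.02% to 2%.

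The reason is simple. The variance of a difference between two visit means is 2σ²(1 − ρ)/n, but a test for independent groups judges it against 2σ²/n. At ρ = 0.5 that reference is twice too large. The stronger the pairing, the more Friedman gains and the more Kruskal-Wallis loses.

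**2. Kruskal-Wallis across arms**

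- At one visit, with all three arms improved by 0.8 SD, it rejects in 4.95% of 4,000 runs. That is the null rate, so it is valid between arms but blind to change within them. It also ignores the baseline score.
- On change scores from baseline (ρ = 0.5, no true difference) it rejects in 5.05% of runs. This is a valid between-arm test, but not one the text specifies.

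**3. Complete cases under classical ANOVA, if nothing is imputed**

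Inputs: 60 randomised; completion c = 0.85 at each follow-up. The article gives 85% as a threshold for assessments in general, so applying it per follow-up visit is an assumption. Baseline is taken as complete because randomisation follows it.

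- The same people miss both visits: 60 × 0.85 = 51 (17 per arm).
- Misses are independent: 60 × 0.85² = 60 × 0.7225 = 43.35, about 43 (14.45 per arm).
- No one misses both: 60 × (1 − 2 × 0.15) = 42 (14 per arm).

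A model that uses anyone with at least one follow-up score would keep 51 in the first case, 60 × (1 − 0.15²) = 58.65, about 59, in the second, and 60 in the third. The gain over complete cases is therefore 0, about 15 or 18 people, depending on the pattern of missed visits.

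**The case against.** **The ITT statement.** A reader might infer that the plan contradicts itself and will drop everyone with a missed visit. The documents do not support this. The article does not say that incomplete cases are excluded. Imputation before the ANOVA would keep all 60, and that detail may sit in a full protocol or SAP that is not shown. What stands is that the named model is complete-case by default, so it fits the stated principle poorly.

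**Kruskal-Wallis between arms.** A reader might infer that the test is unusable here. That also goes too far. With three arms and a between-arm aim it is a natural rank test, and for baseline against one follow-up, comparing change between arms is the arm-by-time contrast. A further simulation on change scores (three arms of 20, ρ of 0.5 and 0.7) gave type I error of 4.4% and 4.3%, and power of 70% and 90% at a 0.8 SD difference. This stands. The text, however, pairs the test with a repeated-measures model and a within-group purpose, and does not mention change scores.

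**The figures.** The across-visit use is one reading, not a stated plan, and its error is conservative, so it would not create false positives. Nor is the lower power of a follow-up-only comparison mainly a fault of the rank test. With one arm shifted by 0.8 SD, Kruskal-Wallis has 69% to 71%, ordinary ANOVA on the same scores 72% to 73%, and baseline-adjusted ANCOVA 85% to 95%. Most of that gap comes from ignoring baseline. The simulations used normal data although the fallback is for non-normal data. This matters little for the table, because both tests use ranks only and are unchanged by any common increasing transformation of the scores. Heavy ties are not covered.

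**Within-group change.** A reader might infer that change within an arm will be presented as the treatment effect. No passage does this: the article calls it preliminary and states a between-arm aim elsewhere.

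**Conclusion.** The point holds in a limited form. The fallback is mismatched to the model it replaces, and its use is unspecified. Across visits it loses much of the information; across arms at one visit it cannot serve the within-group purpose; on change scores it would be sound, but the plan does not say so. The repeated-measures ANOVA could reduce the analysed set from 60 to between 42 and 51 at the trial's own completion threshold, on the condition that nothing is imputed.

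The power and error figures rest on the assumed correlations and the assumed 0.5 SD change; the documents give neither. Severity is moderate. The scales are secondary and meant to inform a later trial, no power was claimed, and the criteria on recruitment, attendance, adherence, adverse events and assessment completion do not depend on these tests.

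**What to change.** For each continuous scale, replace the ANOVA with a linear mixed model:

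- Outcome: the 7-week and 3-month follow-up scores.
- Fixed terms: arm, visit, arm-by-visit and baseline score, with the correlation between a person's two follow-up scores modelled.
- Population: all randomised participants with any post-baseline score, in the allocated arm. State the number in each arm with none, since this model does not recover them.
- Report: between-arm differences with 95% confidence intervals at each follow-up; within-arm change as descriptive only.

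Replace the fallback sentence with a defined alternative for clearly non-normal residuals: a bootstrap or permutation version of the same model, or rank ANCOVA. If Kruskal-Wallis is kept, state that it compares arms on change scores, and use Friedman or Wilcoxon signed-rank for change within an arm.

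The cost is a few sentences in the protocol or SAP, settled before the data are analysed, and slightly more analysis work. No new data are needed.

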### Study procedure

Potential participants will be recruited through ongoing Save the Children Sweden activities in three regions of Sweden (East, South and West). Save the Children Sweden has available programmes for children, young people and caregivers nationally. In 2024, activities reached almost 40 000 children and young people. These programmes included psychosocial activities, group-based mental health support and safe meeting places where displaced persons were able to receive support. Recruiting staff at Save the Children will inform all young people about who may meet the eligibility criteria about the possibility of participating during their regular activities. If recruitment for the final sample size is not possible through ongoing Save the Children services, advertisements will be placed on social media with information about the study. Potential participants who indicate interest in participation are then referred to the study team and perform an initial screening assessment of eligibility using the WHODAS 2.0, K10 and a structured suicide risk evaluation assessment. Participants will be invited to the baseline assessment if they meet the eligibility criteria stated above and consent to participating in the trial. At baseline, participants will complete the following assessments: HSCL-25, PCL-5, PSYCHLOPS, WHO-5, bonding social capital, SHS-A and CSRI. In addition, participants will be asked to complete PMLD and the traumatic event checklists. Following the assessment, participants will be randomly assigned in a consecutive manner, using a 1:1:1 ratio for the randomisation process. The randomisation sequence will be computed by an independent researcher from KI using computerised software and allocation will be conducted by Save the Children Sweden; allocation is concealed from all study staff. Following the completion of the intervention, participants will be invited to complete 1-week postintervention (7-week) and 3-month follow-up (18-week) assessments.

After the 3-month follow-up, participants will be invited to take part in the qualitative process evaluation. Individual semistructured qualitative interviews will be conducted by researchers and psychologists. Interviews with participants and their families will be held in their preferred language. For key informants, interviews will be conducted on an ongoing basis throughout the trial, and for PM+EP/PM+helpers, at the conclusion of their final sessions.

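### The only fallback for non-normal outcomes, Kruskal-Wallis, takes no account of pairing, so the within-arm change that the plan sets out to study has no suitable test when normality fails

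*Protocol article*

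**What the plan says.** The Analysis plan section gives two purposes for the primary analyses. One concerns safety and acceptability; the other is "to preliminarily understand the within-group changes prior to and following the PM+(EP) Interventions". The method follows: "The data will be analysed for the primary outcome and the other continuous measures using repeated measures analysis of variance". The next sentence is the only provision for non-normal data: "Kruskal-Wallis tests will be used if the normal distribution assumption fails". It does not say which score the test is applied to, at which visit, or whether the groups compared are arms or visits. No paired or repeated-measures rank method is named anywhere.

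The design is a "three-armed single-blind randomised controlled parallel group design, comparing PM+, PM+EP and care as usual (CAU"), with allocation "using a 1:1:1 ratio for the randomisation process". On timing, the Trial design section says: "Assessments will be conducted at baseline, 1 week after treatment completion (7 weeks) and 3 months after treatment completion (19 weeks"). Table 1 schedules the symptom, well-being and hope scales at all three visits (T1, T2, T3). On numbers, the Sample size section says: "A total number of 60 forcibly displaced youth (20 in each arm) will be included in the study". It adds that "no formal power calculations have been carried out". The end of the Introduction gives a preliminary comparison of PM+EP with PM+ and with care as usual as a secondary aim.

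**The concern.** Kruskal-Wallis is the rank counterpart of one-way ANOVA on independent groups. The rank counterpart of a one-sample repeated measures ANOVA is Friedman, or the Wilcoxon signed-rank test for two visits. Replacing repeated measures ANOVA by Kruskal-Wallis therefore changes the question as well as the distributional assumption, because the time effect and the arm-by-time effect disappear.

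An analyst who follows the sentence literally can compare visits within an arm, treating one person's three scores as coming from three people. Or the analyst can compare arms, which leaves the before-after question within each arm unanswered. The secondary outcomes are meant to indicate possible effectiveness and to prepare a definitive trial (Secondary outcome measures section). A real within-arm change that is missed, or never tested, would weaken that use.

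**Working it through.** **Inputs from the article.** Three arms, 20 per arm (3 × 20 = 60), three visits per participant. The article gives no power, alpha, effect size or SD, so there is no stated figure to reproduce.

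**Assumptions, not document values.** Alpha 5%; equal within-person correlation ρ between visits, 0.3 to 0.7; a true change of 0.5 SD.

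**Use 1: across the three visits within one arm.** Kruskal-Wallis ranks all N = 20 × 3 = 60 scores together:

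H = 12/[N(N+1)] × Σ(R_j²/n_j) − 3(N+1), with k = 3 groups, referred to chi-square on k − 1 = 2 df.

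That reference distribution assumes 60 independent scores. With paired scores, the variance of a difference between two visit means is 2σ²(1−ρ)/n, not 2σ²/n, so under the null H behaves roughly like (1−ρ) times a chi-square on 2 df. The 5% critical value is 5.991, and the upper tail of that chi-square beyond x is exp(−x/2). The actual type I error is therefore roughly exp[−2.996/(1−ρ)]:

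- ρ = 0.4: exp(−4.99) ≈ 0.7%
- ρ = 0.6: exp(−7.49) ≈ 0.06%
- ρ = 0.7: exp(−9.99) ≈ 0.005%

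This is a large-sample approximation that explains the direction. Simulation at n = 20 gives:

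| Scores | ρ | Type I error, Kruskal-Wallis | Type I error, Friedman | Power at 0.5 SD, Kruskal-Wallis | Power at 0.5 SD, Friedman |
|---|---|---|---|---|---|
| Normal (2000–3000 runs) | 0.4 | 1.2% | 5.7% | 22% | 39% |
| Normal | 0.6 | 0.2% | 4.4% | 19% | 57% |
| Normal | 0.7 | 0.0% | 5.1% | 18% | 70% |
| Log-normal (4000 runs) | 0.3 | 1.5% | 5.7% | 27% | 37% |
| Log-normal | 0.5 | 0.6% | 5.3% | 22% | 46% |
| Log-normal | 0.7 | 0.05% | 5.9% | 17% | 71% |

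In the log-normal runs the SD is on the log scale and the change is present at both follow-ups. Wilcoxon signed-rank, baseline against first follow-up, has type I error 4.8 to 5.2% and power 40%, 52% and 74% at ρ = 0.3, 0.5 and 0.7.

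Kruskal-Wallis and Friedman both use only the order of the scores, so the same increasing transformation of every score leaves them unchanged. Skewness of the log-normal kind therefore cannot alter their rows; the two sets differ only in ρ and in simulation error. Heavy ties at the floor or ceiling of a scale were not simulated.

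**Use 2: across the three arms, on a change score or at one visit.** Each participant contributes one value, so N = 60 independent values and the test is valid. But if change has the same distribution in every arm, H has its null distribution whether the common change is nil or large. The simulation agrees: on change scores, with every arm improving by 0, 0.5 or 0.8 SD (ρ = 0.5 or 0.7), the rejection rate is 4.7 to 5.2% throughout. The test carries no information on within-arm change.

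**Side by side.** Use 1 addresses the within-group purpose with the wrong error rate and low power. Use 2 is sound but addresses only the between-arm aim.

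**The case against.** The strongest defence is that Kruskal-Wallis was meant for comparing the arms. On a change score across three randomised arms it is a legitimate test with about 5% type I error, it serves the secondary aim, and for one follow-up it acts as a rank analogue of the arm-by-time contrast. This stands. A reader might infer that every way of applying the test to these data is invalid; the documents do not support that. What remains is that the article does not state this use, and that it would still leave within-arm change without a test.

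A reader might also infer inflated false positives. If all 60 × 3 = 180 scores were pooled and compared by arm, simulated type I error would be 19%, 25% and 29% at ρ = 0.4, 0.6 and 0.7. Nothing in the article says scores will be pooled in this way, so these figures do not describe the plan. The across-visit use errs in the other direction: it loses power and does not create false signals.

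It is fair to add that no power is claimed, that the article does not say how normality is judged or whether outcome by outcome, and that how often the fallback would be used is unknown. A mean-based Cohen's d beside a rank test is a descriptive choice and not an error.

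A separate analysis plan, not seen here, may say more. That does not remove the point, because the article itself names this test as the replacement.

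**Conclusion.** The point holds as a mismatch between the stated fallback and a stated purpose of the analysis. When normality fails, within-arm change is either not tested, or is tested at about 0 to 1% instead of 5%, with power of about 18 to 22% against 39 to 70% for Friedman. Those ranges rest on 20 per arm, three visits, equal correlations of 0.4 to 0.7 and a 0.5 SD change; only the first two come from the article. The structural part, that Kruskal-Wallis has no subject or time term, needs no assumption.

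Severity is moderate. It may be tempting to conclude that the trial's main result is at risk, but the documents do not support that. The Feasibility measures section judges feasibility by thresholds for recruitment and consent (>70%), attendance (>70%), helper adherence (>75%), adverse events (<10%) and completed assessments (>85%), and none calls on this test. The symptom comparisons are described as preliminary.

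**What to change.** Replace the Kruskal-Wallis sentence with a rule that separates the two questions for non-normal outcomes:

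- Within-arm change: Wilcoxon signed-rank for T1–T2 and T1–T3, with a Hodges-Lehmann interval, or Friedman over the three visits. Friedman uses only participants with all three visits, while the signed-rank test needs only the pair concerned.
- Between-arm comparison: Kruskal-Wallis on a named change score, such as T2 minus T1, and never on repeated scores pooled over visits.

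One linear mixed model for each outcome would be a reasonable alternative, but that is a preference and is not needed to cure the defect. The cost is one sentence in the analysis plan, with no new data, staff or participants.

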### Feasibility measures

The primary outcome of this study will be the feasibility and acceptability of the delivery of PM+EP in refugee youth. Feasibility will be determined through criteria related to consent and recruitment rates (>70%), attendance to PM+/PM+EP sessions (>70%), protocol adherence by helpers (>75%) and the number of AEs (<10%). In this study, AEs were defined as any unwanted experiences during the study, regardless of relation to PM+or PM+EP. Serious AEs (SAEs) are events causing death, life threat, hospitalisation or its prolongation, permanent disability or other significant medication conditions not necessarily connected to the intervention. All AEs/SAEs will be reported and followed, with specialist referral as needed. Regarding the feasibility of the research procedure, the completion of the baseline and follow-up assessments will be assessed (>85%). In addition, the qualitative process evaluation will further elucidate information of the acceptability of the interventions.

Protocol adherence will be determined through two methods. The first is a self-rated fidelity checklist that the PM+/PM+EP facilitators will fill out at the end of each session. This will contain each of the elements from the completed session, and facilitators will be asked to identify what items they completed and which items they may have missed to assess the degree of fidelity to the manualised intervention. second, audio recordings of sessions will be taken if participants provide informed consent for recording. A random sample of 10% of recordings will be scored independently by two research assistants.

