### Secondary outcome measures

Secondary outcome measures will be administered at baseline and follow-up assessments to inform about possible effectiveness and preparation for a future definitive trial of PM+EP. The Hopkins Symptom Checklist-25 (HSCL-25) is a 25-item validated psychometric scale assessing symptoms of depression (15 items) and anxiety (10 items).^35^ Two of the depression items specifically relate to associated somatic symptoms. The items are rated on a 4-point Likert scale (range=25–100), ranging from 1 (not at all) to 4 (extremely).

PTSD symptom severity and diagnosis will be established with the PTSD Checklist for DSM-5 (PCL-5).^36^ The PCL-5 is a 20-item checklist, corresponding to the 20 symptoms of PTSD as described in the Diagnostic and Statistical Manual of Mental Disorders, Fifth Edition (DSM-5). Each item is scored on a 5-point scale, ranging from 0 (not at all) to 4 (extremely). When the symptom severity score is rated as two (moderate/threshold) or higher, a symptom is considered present. Total symptom severity is calculated by summing the scores of the 20 items (range: 0–80), with higher scores indicating worsened severity of post-traumatic stress symptoms.

The Psychological Outcomes Profiles (PSYCHLOPS) will be used to indicate the client’s perspective of change in their psychological distress level after therapy.^37^ PSYCHLOPS has four questions measuring three domains; the problem(s) bothering the individual (two questions), and how these problems affect the daily functioning and well-being. Scores range from 0 to 5 and higher scores represent more psychological difficulty (range=0–20).

Social support will be measured through a 1-item question assessing ‘bonding social capital’ from the Stockholm Public Health Cohort.^38^ Participants will be asked: ‘Do you know any people who can provide you with personal support for personal problems or crises in your life?’. The response will be categorised as either high social support or low social support.

The Client Service Receipt Inventory (CSRI)^39^ will be used to track the healthcare service use and medications that the participant has received in the 3 months preceding their entry to the study and over the course of the study.

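### The preliminary effectiveness output is hypothesis tests plus a Cohen's d tied to a feasibility outcome; with 20 per arm it should be named between-arm differences and d with 95% intervals

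*Protocol article*

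**What the plan says.** The Analysis plan assigns repeated measures ANOVA to the primary outcome and the other continuous measures, and adds that "Kruskal-Wallis tests will be used if the normal distribution assumption fails". It uses intention-to-treat analyses to estimate potential effectiveness for a future trial. It closes with a Cohen's d on the pooled SD, which "will be used to calculate the treatment effect size of the PM+EP (based on primary outcome".

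Under Feasibility measures, the primary outcome is the feasibility and acceptability of delivering PM+EP. Feasibility is judged by percentage thresholds for consent and recruitment, attendance, helper adherence, adverse events and assessment completion.

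The symptom and well-being scales are secondary. They are collected "to inform about possible effectiveness and preparation for a future definitive trial of PM+EP" (Secondary outcome measures).

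On size, the Sample size section says "A total number of 60 forcibly displaced youth (20 in each arm) will be included in the study", that "no formal power calculations have been carried out", and that the number rests on earlier similar studies. The Introduction describes the comparison of PM+EP with PM+ and usual care as preliminary and as a secondary aim.

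**The concern.** There are two problems in the same short paragraph.

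First, d is attached to an outcome for which it cannot be computed as described. A Cohen's d on a pooled SD needs a continuous score, two groups and a visit. The named outcome is a set of percentage criteria together with qualitative findings on acceptability. No symptom score is designated in its place, and no comparator or time point is named. Several different d values would fit the sentence equally well, and the choice could be made after the data are seen.

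Second, the stated output does not suit the stated purpose. A test in an unpowered three-arm pilot gives a p-value that cannot separate no effect from too few participants. A point d from 20 versus 20 does not show how uncertain it is. Whoever prepares the definitive trial needs the range of effects compatible with the data, the SDs, and the correlation between baseline and follow-up.

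**Working it through.** **Inputs from the protocol.** 60 participants, 20 per arm (Sample size); 1:1:1 allocation (Study procedure); assessment completion threshold above 85% (Feasibility measures); follow-up at T2 and T3 (Table 1). The arm sizes agree with the total: 3 × 20 = 60. No power figure is stated, so there is none to reproduce.

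**Assumptions made here.** Two-sided 5% level, because the protocol sets none, and true standardised differences of 0.3, 0.5 and 0.8. The main calculation is a two-arm, single-visit t comparison. That approximates the plan and is not the repeated measures ANOVA itself.

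**1. How many d values fit the sentence?** The continuous secondary scores are HSCL-25 depression, HSCL-25 anxiety, PCL-5, PSYCHLOPS, WHO-5 and the hope agency subscale, which makes 6. PM+EP can be compared with PM+ or CAU (2), at T2 or T3 (2). That gives 6 × 2 × 2 = 24 candidates, none of which is the primary outcome.

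**2. Power of a pairwise test.** Non-centrality = d × √(n/2), with 2n − 2 degrees of freedom. At n = 20 and d = 0.5 this is 0.5 × √10 = 1.58 with 38 df.

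| True d | 20 per arm | 17 per arm (0.85 × 20) |
|---|---|---|
| 0.3 | 15% | 14% |
| 0.5 | 34% | 29% |
| 0.8 | 69% | 62% |

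80% power needs d = 0.91 at 20 per arm and 0.99 at 17.

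**3. Does the approximation matter?** Adjusting for baseline at 20 per arm multiplies the SD by √(1 − r²). Under a normal approximation, power at d = 0.5 rises from 35% to 45% (r = 0.5) or 60% (r = 0.7). A three-arm omnibus test at one visit, with means 0, d/2 and d, has 26% power at d = 0.5 and 59% at d = 0.8. No version reaches 80% at d = 0.5.

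**4. Precision of d.** SE(d) = √(2/n + d²/(4n)). At n = 20 and d = 0.5: √(0.100 + 0.003125) = 0.321. The 95% CI is 0.5 ± 1.96 × 0.321, or -0.13 to 1.13; the exact noncentral-t interval agrees to two decimals. At 17 per arm the exact interval is -0.19 to 1.18. An observed 0.8 at 20 per arm gives 0.15 to 1.44.

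**5. Selecting on significance.** At 20 per arm an observed d must exceed about 0.64 to be significant. In simulation, the significant results favouring PM+EP average about 0.87 when the true d is 0.5, and 0.82 when it is 0.3.

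**6. What the pilot can estimate better.** A pooled SD across three arms has 60 − 3 = 57 df. Its 95% chi-square limits are 0.845 to 1.224 times the estimate, or about -15% to +22%.

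**The case against.** The strongest reply is that this is a declared feasibility trial and the text is cautious. The comparison is called preliminary and secondary, effectiveness is called possible or potential, and no significance level is set. A feasibility trial needs no power calculation, so low power follows from an acceptable design. All of this stands.

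It also limits what can be claimed. A reader might infer that the results will be over-read, or that a non-significant test would stop the module. The documents support neither: the feasibility criteria are percentages, and none depends on a p-value or on d. A reader might also infer that the pilot's d will size the next trial. The protocol does not say so, and the planning quantity named under Sample size is drop-out. How the definitive trial chooses its target difference belongs to that trial's protocol.

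A further reply is that this is a condensed article, and that intervals, multiplicity handling, and the comparator and visit for d may be set out in a fuller plan. That is fair, and silence on them is not counted as an error here. Nor can it be said that SDs would go unreported, since d on a pooled SD requires one.

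What the reply does not remove is the stated text. The article chooses tests as the method for the continuous measures, and it attaches d to the primary outcome. Extra detail elsewhere would not reconcile that link with a feasibility outcome.

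**Conclusion.** The point holds as a modest, inexpensive improvement to a stated method. The link between d and the primary outcome is a mis-specification on the face of the document and depends on no assumption. The limited value of tests and a point estimate depends on 20 per arm, an assumed two-sided 5% level and a simplified two-arm, single-visit comparison. Under those, a non-significant result says little about effects of 0.5 (34% power) or even 0.8 (69%), and an observed d of 0.5 is compatible with anything from slight harm to a very large benefit. Baseline adjustment improves this without changing the conclusion at d = 0.5. Misreading is therefore a possibility worth closing off. It is not a documented outcome, and neither the feasibility aims nor the sample size is called into question.

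**What to change.** Reword the effectiveness part of the Analysis plan so that it rests on estimation:

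- Replace the reference to the primary outcome with the continuous secondary scores by name.
- For each score, report the between-arm difference and Cohen's d for PM+EP versus PM+ and for PM+EP versus CAU, at T2 and T3, each with a 95% CI.
- Report the SDs and the baseline-follow-up correlations alongside.
- Label any p-values from the ANOVA or Kruskal-Wallis tests as exploratory, and state that no conclusion on effectiveness will be drawn from them.

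The cost is a few sentences; no extra participants, visits or data are needed. The downside is that the pilot will have no headline p-values to quote.
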